### Sample size considerations

Sample size calculations are based on recommendations from Hayen et al. for DTA studies [31]. Weighed means of sensitivity and specificity of BS, SPECT/CT and ^18^F-fluoride PET/CT were calculated based on reported values in published clinical trials. The power calculation showed that 114 patients are needed to identify a significant difference between the false positive fractions (i.e., 1-specificity) of BS and SPECT/CT versus ^18^F-fluoride PET/CT with a type I error of 5 % and a type II error of 20 %, assuming a prevalence of bone metastases of 50 % on BS. A total of 140 patients will be recruited to account for possible dropouts. Calculated weighed mean values of true positive fractions (sensitivity) for BS, SPECT/CT and ^18^F-fluoride PET/CT are very similar (0.87, 0.90, and 0.87, respectively), which indicated that more than 5,000 patients were needed to demonstrate a significant difference in sensitivity among the methods.

### Data analysis

A detailed statistical analysis plan, including considerations for secondary endpoints, will be issued prior to analysis. Data analysis will primarily focus on the diagnostic accuracy of BS and ^18^F-fluoride PET/CT. Sensitivity, specificity, positive and negative predictive values, and likelihood ratios will be calculated for each imaging modality with 95 % confidence intervals and will be compared using the McNemar test, with *P* < 0.05 being statistically significant.

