## Methods/Design

### Study objectives

The primary objective of this study is to assess the diagnostic accuracy of ^18^F-fluoride PET/CT for detection of bone metastases compared with BS in newly diagnosed, high risk, untreated prostate cancer patients on an individual patient basis.

Secondary objectives are: 1) to assess the diagnostic properties of SPECT/CT in comparison with BS and ^18^F-fluoride PET/CT, 2) to evaluate the diagnostic properties of all imaging modalities on the basis of individual lesions, 3) to investigate the inter- and intra-observer variation of SPECT/CT and ^18^F-fluoride PET/CT, and 4) to investigate the predictive role of bone tumour load as measured by ^18^F-fluoride PET/CT as a predictor of time to loss of hormone sensitivity.

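### McNemar's test is named for comparing predictive values and likelihood ratios, to which it does not apply; it is valid only for patient-level sensitivity and specificity

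*Protocol article*

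**What the plan says.** The Data analysis section of the protocol article states: "Sensitivity, specificity, positive and negative predictive values, and likelihood ratios will be calculated for each imaging modality". The same sentence goes on to say that these will have 95% "confidence intervals and will be compared using the McNemar test", with significance at P < 0.05. The grammatical subject of the comparison is the whole list, and the article names no other comparison test.

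That section also says that a detailed SAP, covering secondary endpoints among other things, will be issued before analysis. Image analysis makes the patient the primary unit. Sample size considerations powers the study on the false positive fraction (1 − specificity): "The power calculation showed that 114 patients are needed", "with a type I error of 5"% "and a type II error of 20"%, "assuming a prevalence of bone metastases of 50"% on bone scintigraphy (BS).

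**The concern.** McNemar's test needs one common set of subjects, each with a binary outcome under both tests. Sensitivity (all reference-positive patients) and specificity (all reference-negative patients) meet that condition. Predictive values do not, because each is conditional on the result of its own scan. Likelihood ratios do not, because they are not proportions.

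An analyst who follows the sentence literally has no valid calculation for PPV, NPV, LR+ or LR−. The analyst must then either run McNemar on some other pairing and label the p-value as a predictive-value comparison, or choose a method once the data are in hand. The first misleads. The second gives up the protection of pre-specification. The measures concerned belong to the main BS versus PET/CT comparison, although they are not the ones the study is powered on.

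**Working it through.** **1. The plan's own figure.** The 114 cannot be reproduced, because the article prints neither the false positive fractions (FPF) nor the discordance. It can be back-solved. At 50% prevalence, 114 × 0.5 = 57 reference-negative patients (this takes the 50% expected on BS as the reference-standard prevalence). The paired formula is

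n = [1.96√ψ + 0.842√(ψ − d²)]² / d²,

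with d the FPF difference and ψ the discordant proportion. If BS has FPF 0.30 (assumed), n = 57 corresponds to a PET/CT FPF of 0.168 at minimum discordance, 0.089 under conditional independence and 0.077 at maximum discordance. So 114 is attainable, and it concerns a quantity for which McNemar is valid. Recruiting 140 implies 1 − 114/140 = 18.6% dropout. Nothing below changes either number.

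**2. Predictive values: different denominators.** Take 57 + 57 patients and sensitivity 0.87 for both scans (from Sample size considerations), with FPF 0.30 for BS and 0.10 for PET/CT (assumed).

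- True positives, each scan: 57 × 0.87 = 49.59
- BS: false positives 57 × 0.30 = 17.1; positives 66.69; PPV 49.59/66.69 = 0.744
- PET/CT: false positives 57 × 0.10 = 5.7; positives 55.29; PPV 49.59/55.29 = 0.897

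With FPFs of 0.40 and 0.20 instead, the PPVs are 0.685 (72.39 positives) and 0.813 (60.99 positives). In both cases the two PPVs rest on different, only partly overlapping sets of patients.

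**3. Predictive values: no discordant pairs.** The only patients who contribute to both PPVs are those positive on both scans. The outcome being compared is whether the patient truly has metastases, and that is one fact per patient. Both off-diagonal cells are therefore zero, and (b − c)²/(b + c) = 0/0. Patients positive on one scan only have no pair. The same holds for NPV among patients negative on both scans. This step needs no assumed figure.

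**4. Likelihood ratios.** LR+ = sensitivity/(1 − specificity) and LR− = (1 − sensitivity)/specificity. Numerator and denominator come from different patients, so there is no single 2×2 table of pairs to test.

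**5. What a substitute McNemar would test.** Assume sensitivity/specificity of 0.90/0.70 for one scan and 0.60/0.80 for the other, 50% prevalence, N = 114 and conditional independence. Then LR+ = 0.90/0.30 = 0.60/0.20 = 3, and both PPVs are 3/(3 + 1) = 0.75. There is no PPV or LR+ difference to find.

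- Test positivity: b = (0.9×0.4 + 0.3×0.8)/2 = 0.30; c = (0.1×0.6 + 0.7×0.2)/2 = 0.10; d = 0.20; ψ = 0.40.
- Correctness: b = (0.9×0.4 + 0.7×0.2)/2 = 0.25; c = (0.1×0.6 + 0.3×0.8)/2 = 0.15; d = 0.10; ψ = 0.40.

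The approximate rejection rate is Φ[(d√114 − 1.96√ψ)/√(ψ − d²)]:

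- Positivity: Φ[(2.135 − 1.240)/0.600] = Φ(1.49) ≈ 93%
- Correctness: Φ[(1.068 − 1.240)/0.624] = Φ(−0.28) ≈ 39%

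Simulation (20,000 trials) gave 94% and 40%. The rates depend on how the two scans agree:

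| Discordance | ψ | Positivity | Correctness |
|---|---|---|---|
| Minimum | 0.20 | Φ(3.15) > 99% | Φ(0.44) ≈ 67% |
| Conditional independence | 0.40 | 93% | 39% |
| Maximum | 0.50 | Φ(1.11) ≈ 87% | Φ(−0.45) ≈ 32% |

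These are not faults of McNemar. Positivity rates (0.60 v 0.40) and overall accuracy (0.80 v 0.70) do differ. The error would lie in reporting those p-values as comparisons of PPV or LR+.

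**The case against.** The sentence is a one-line summary in a condensed article. It may be shorthand for comparing the modalities by McNemar where that test applies, with measure-specific methods left to the announced SAP. Predictive values and likelihood ratios appear once, in a list, with no power claim and no objective of their own. They can still be estimated with 95% intervals. LR+ and LR− are functions of sensitivity and specificity, so the core comparison survives without p-values for them. The misuse in step 5 of the working is hypothetical; the article does not describe it.

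Most of this stands, and it limits the severity. It does not remove the point. Read as printed, the sentence names a test for the full list, and deferring detail to an SAP does not repair a method already named that cannot be carried out.

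A reader might go further and infer that McNemar, as the only test named, will also be applied to lesions as if they were independent within a patient, since a secondary objective is "to evaluate the diagnostic properties of all imaging modalities on the basis of individual lesions". The article does not support that. Image analysis makes the analysis primarily patient-based, summarises lesions to one result per patient, and leaves patients with multiple lesions to the reader manual and SAP. Data analysis leaves secondary endpoints to the SAP. Nothing prescribes an unadjusted McNemar test on lesions, and any estimate of error inflation would need lesion counts and a within-patient correlation that the article does not give.

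**Conclusion.** The point holds for PPV, NPV, LR+ and LR−: the named test does not apply to them, and the planned p-values cannot be produced. This follows from the structure of the test and rests on no assumption. The PPVs in step 2 of the working and the rejection rates in step 5 are illustrations; the FPFs, the step 5 sensitivities and specificities, and conditional independence are assumed.

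Severity is low to moderate. McNemar is valid for patient-level sensitivity and specificity, so the powered false positive fraction comparison, the 114 evaluable patients and the 140 to be recruited are untouched. It would be wrong to infer that the main specificity result or the sample size is at risk. Lesion clustering is no part of this finding.

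**What to change.** Reword the Data analysis sentence, or state in the SAP before analysis that it is superseded:

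- **Sensitivity and specificity (patient level):** McNemar's test, with the paired difference and its 95% interval.
- **PPV and NPV:** a paired predictive-value method, such as the weighted generalised score test, or GEE for disease status with one record per positive (for NPV, negative) scan and the patient as cluster.
- **LR+ and LR−:** the ratio between modalities, with a patient-level bootstrap or log-scale delta-method 95% interval; or each modality's value with its interval and no test.

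Name one option per measure, so that the choice does not depend on the data. The cost is a few sentences and a few lines of code, with no new patients, scans or readings.

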### Quality assessment

All scans are performed according to local practices which are in line with international guidelines [29]. No detailed requirement for accreditation of the equipment prior to baseline is applied. However, the image quality of the applied scanners is compared in order to adjust for any relevant differences in scanner performances in the statistical analysis. The following performance measurements will be obtained: data from the initial installation of the scanner, data from the most recent quality control, and prospective, study-related data from phantom scans.

### Rationale for design

#### Patient selection

The GRADE recommendations state that valid DTA studies should include representative and consecutive patients [15]. This study is conducted in bone-metastasis-enriched patients with prostate cancer due to the ADT-assisted definition of the presence or absence of bone metastasis. However, inclusion of low-risk patients as well as patients undergoing curatively intended treatment would interfere with sample size calculations and/or methodological issues with regard to the validity of the reference standard. For example, persistently elevated PSA levels following radical prostatectomy may arise from the remnant primary tumour or lymph nodes, as well as bone metastases. In addition, the PSA response in patients receiving curatively intended radiation therapy may be very slow, may be masked by concomitant ADT; any progression some years after post-therapy cannot be attributed with certainty to bone metastases at the time of diagnosis.

### DTA design

This DTA protocol and the planned manuscript is and will be in full compliance with the 25 items of the STARD guideline, including title and abstract, introduction, methods (participants, test methods, statistical analysis), and results. Similar to the CONSORT statement of reporting of randomised controlled trials and the PRISMA statement for reporting of systematic reviews (see www.equator-network.org), STARD is a guideline for reporting of DTA studies. The trial methodology laid down in the STARD recommendations have also been endorsed by the Cochrane organisation for systematic reviews of diagnostic test studies. It is generally accepted that properly conducted DTA trials are a requirement before the conduct of randomised controlled trials to study the impact of different diagnostic strategies on patient outcome [15, 32]. This DTA study is completely compliant with STARD criteria [14]. Compliance with and reporting of STARD items in DTA studies has been slowly increasing since the introduction of STARD; however, according to Korevaar et al., as of 2014, reporting of STARD could still be improved [33].

According to GRADE, patient-important outcomes can be inferred on the basis of diagnostic test accuracy. This means that if this DTA study demonstrates that the diagnostic accuracy is significantly improved by ^18^F-fluoride PET/CT compared with BS then more cases of prostate cancer will be correctly classified according to disease stage, thus ensuring optimal management of the disease. On the contrary, if the diagnostic accuracy is equal for both modalities but ^18^F-fluoride PET/CT is more convenient for the patient (e.g., shorter time from injection to scan and shorter scan time), these results will ensure that the course of diagnosis is optimal.

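### The protocol attaches a conclusion to equal accuracy, but its stated design (a test of difference, sized on specificity) cannot support equality of sensitivity

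*Protocol article*

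**What the plan says.** The section *DTA design* (under Rationale for design) describes two ways in which the results are to benefit patients. In the first, accuracy is significantly improved by PET/CT. In the second, "if the diagnostic accuracy is equal for both modalities" and PET/CT is more convenient, and then "these results will ensure that the course of diagnosis is optimal".

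*Data analysis* names the accuracy measures (sensitivity, specificity, predictive values, likelihood ratios). They "will be calculated for each imaging modality with 95 % confidence intervals" and "will be compared using the McNemar test", with P < 0.05 as the threshold. No interval for the difference between modalities is mentioned.

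*Sample size considerations* derives 114 patients (140 recruited) from a difference in false-positive fractions, with 5 % type I and 20 % type II error and a 50 % prevalence of metastases on bone scintigraphy (BS). Pooled sensitivities are given as 0.87 for BS, 0.90 for SPECT/CT and 0.87 for PET/CT. From these the authors conclude that "more than 5,000 patients were needed to demonstrate a significant difference in sensitivity among the methods".

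No equivalence or non-inferiority margin, and no definition of equal accuracy, appears in the article.

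**The concern.** The second route in *DTA design* is an affirmative conclusion drawn from equality. A test of difference can reject equality but cannot establish it; for that one needs an interval for the difference and a margin. The primary objective is diagnostic accuracy, which includes sensitivity. The authors expect the two sensitivities to be the same and did not size the study on them. A non-significant sensitivity comparison is thus a likely outcome, and nothing in the stated analysis says how it may be interpreted.

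At stake is a statement that PET/CT is as accurate as BS, and preferable for convenience, when the data remain compatible with a loss of sensitivity that clinicians would care about.

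**Working it through.** **The plan's own figures.** The 114 cannot be reproduced, because the false-positive fractions behind it are not printed. The figure above 5,000 cannot be tied to one comparison:

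- SPECT/CT against BS or PET/CT (0.90 against 0.87): n = [1.96·√ψ + 0.842·√(ψ − d²)]²/d², divided by 0.5, with d = 0.03. This gives 519 to 4,007 patients in total, from minimal to maximal discordance ψ. An unpaired formula gives 7,096.
- BS against PET/CT (0.87 against 0.87): the difference is zero, so no finite number exists.

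The figure therefore describes nearly equal assumed sensitivities, not a difference of clinical concern. The relevant question is what 114 to 140 patients can say about such a difference.

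**Inputs.** Metastatic patients: 0.50 × 114 = 57, or 0.50 × 140 = 70 if all are evaluable. Sensitivity: 0.87 for both. The test is taken as two-sided. Discordance ψ (the share of metastatic patients classified differently by the two scans) is not in the article and is an assumption: 5 %, 10 %, or 2 × 0.87 × 0.13 = 22.6 % (independent errors).

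**Precision.** The half-width of the 95 % interval for the paired difference, when sensitivities are equal, is 1.96·√(ψ/n).

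| ψ | n = 57 | n = 70 |
|---|---|---|
| 5 % | 5.8 points | 5.2 points |
| 10 % | 8.2 points | 7.4 points |
| 22.6 % | 12.3 points | 11.1 points |

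**Power of McNemar's test for a true loss with PET/CT, n = 57.** This is summed over the number of discordant pairs. Under independence, ψ = 0.87(1 − s) + s(0.13), where s is the PET/CT sensitivity. Under maximal agreement, ψ equals the loss and every discordant pair goes one way.

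| PET/CT sensitivity | Independent errors: exact / asymptotic | Maximal agreement: exact / asymptotic |
|---|---|---|
| 0.82 | 7 % / 11 % (ψ = 0.263) | 6 % / 32 % (ψ = 0.05) |
| 0.77 | 21 % / 28 % (ψ = 0.300) | 51 % / 83 % (ψ = 0.10) |

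With 70 metastatic patients, the 10-point loss has 26 % / 34 % power under independence, and 71 % exact power under maximal agreement.

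**Illustration.** Suppose 8 metastatic patients are found only by BS and 2 only by PET/CT. Exact p = 2 × P(X ≤ 2 | 10, 0.5) = 0.11, and the chi-square is (8 − 2)²/10 = 3.6, below 3.84. The result is not significant. Yet the estimated loss is 6/57 = 10.5 points, with a Wald 95 % interval of about 0 to 21 points.

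**What a margin would allow.** Power to exclude a loss of size M when the true difference is zero is Φ(M/√(ψ/57) − 1.96). The margins are illustrative, since the article gives none.

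| M | Power over ψ = 22.6 % to 5 % |
|---|---|
| 5 points | 12 to 39 % |
| 10 points | 36 to 92 % |
| 15 points | 66 to 99.9 % |

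For 80 % power at 10 points, ψ may be at most 0.10² × 57/(1.96 + 0.842)² = 7.3 %.

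**The case against.** The strongest reply is that the sentence on equal accuracy is part of a rationale, introduced with reference to GRADE, and is not a decision rule. That is so. A reader might infer that the protocol declares non-significance to mean equality, but the text does not say this. What stands against the reply is that the article gives no other criterion by which equality could be established.

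A reader might also infer, from the figure above 5,000, that a non-significant sensitivity result is assured whatever the truth. The documents do not support that. The figure belongs to the assumed, nearly identical sensitivities. A 10-point loss would be detected 51 to 83 % of the time under maximal agreement, and a 15-point loss (0.87 to 0.72) has exact power of 42 % under independence and about 87 % under maximal agreement. Independent errors are also an unfavourable assumption, since the Background calls the principle of the two tracers somewhat similar. The truth may lie nearer the agreement end.

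Confidence intervals are planned, so imprecision will be partly visible. But separate intervals for each modality do not give the uncertainty of a paired difference.

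The limited power for sensitivity is openly disclosed. A statistical analysis plan is announced and could add a margin. The hierarchy among accuracy measures, and any multiplicity across them, properly belong there and are not part of this point. A later plan would not, however, correct the published sentence or change the sample size.

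**Conclusion.** The point holds in a limited form. As stated, the design cannot support a conclusion of equal sensitivity, although the article attaches a conclusion to equal accuracy. With about 57 metastatic patients, the paired sensitivity difference will be known to within roughly 6 to 12 points (5 to 11 with 70). A non-significant result is likely for a 5-point loss (exact power 6 to 7 %, asymptotic 11 to 32 %). It is also likely for a 10-point loss unless the two scans agree closely.

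This rests on sensitivity 0.87, on the assumed discordance range, and on 50 % prevalence. The prevalence is stated for BS, whereas the final diagnosis counts a malignant lesion on any modality, so the number with metastases may differ from 57. The powered comparison of false-positive fractions is not affected.

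**What to change.** Keep patient-level specificity of PET/CT against BS as the powered comparison. For sensitivity, report the paired difference, PET/CT minus BS, with a 95 % confidence interval. Fix and justify a margin before the data are analysed. Use equal or not worse only if the interval excludes that margin; otherwise write that the study is inconclusive for sensitivity. Reword the sentence in *DTA design* so that the convenience argument depends on this criterion, and state that a non-significant McNemar test will not be read as equality.

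The cost is wording in the protocol and analysis plan, with no added patients. The drawback is that sensitivity will probably have to be reported as inconclusive: a 5-point margin is out of reach at this size, and a 10-point margin has 80 % power with 57 metastatic patients only if discordance is about 7 % or less.

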## Discussion

Early and correct diagnosis of bone metastases in prostate cancer is important for clinical decision making. Thus, sensitive and specific diagnostic techniques are required. BS remains the guideline-recommended method for staging of bone metastasis in prostate cancer, but it can be debated if this is appropriate in light of emerging, interesting methods such as ^18^F-fluoride PET/CT and multi-parametric magnetic resonance imaging [34].

The decision to select an appropriate diagnostic method preferably should be made based on evidence-based recommendations. However, in 2011, Poonacha et al. [35] published a study examining the level of evidence underlying clinical recommendations from the National Comprehensive Cancer Network. It was revealed that no recommendations for prostate cancer staging, as well as for any other diagnostic recommendations across tumour types, were based on level I evidence. Small series and retrospective studies have indicated that ^18^F-fluoride PET/CT is significantly better than BS; however, the superiority of ^18^F-fluoride PET/CT remains to be shown in properly designed and well-powered clinical trials [9, 13, 36–38]. The level of evidence among previously published studies is quite low (level 3b according to the Oxford Centre for Evidence-based Medicine) [10]. The low level of evidence in diagnostic medicine is a general phenomenon [35], but the issues have been highlighted on several occasions regarding imaging [33]. We believe that a large DTA study performed in accordance with STARD recommendations will allow us to make firm conclusions about the diagnostic properties and potential advantages of ^18^F-fluoride PET/CT versus guideline-recommended BS.

We realise that strict methodological criteria and high quality procedures may conflict with generalisability of the findings in clinical practice. Therefore, images are read with key clinical information as would be available in clinical situations. The risk of reading bias is present but the reading conditions are fully described; thus, all stakeholders can judge the results based on his or her premises. Similarly, gamma cameras and PET/CT scanners are not accredited or standardised prior to recruitment as required in some multicentre trials, e.g., those from the European Organization on Research and Treatment of Cancer. Instead, we aimed at comparing the imaging modalities as they are used in daily clinical practice rather than comparing the imaging modality per se under optimal instrumental settings.

^18^F-fluoride PET/CT has already been routinely applied for detection of bone metastases in prostate cancer in some clinics. However, it is important to note that in the most recent guidelines from the National Comprehensive Cancer Network on prostate cancer, panelists express their concern about the inappropriate use of expensive PET imaging in the clinical setting [39], e.g., ^18^F-fluoride PET/CT for the staging of prostate cancer. Thus, there is a rationale for conducting properly designed DTA studies before making changes in clinical practice. If superiority is clearly evident, the work required to demonstrate it is limited. The design and size of this study ensure that the results will be recognised both nationally and internationally; the perspective may be the general use of ^18^F-fluoride PET/CT for bone imaging in prostate cancer.

